#### Descriptive Outcomes:

Descriptive statistics and confidence intervals for the change from baseline to one month follow-up and to three month follow-up for each of the two treatment groups will be provided for each of the descriptive outcome measures. Additionally, comparisons between mifepristone and placebo will be performed; however, lack of statistical significance should not be construed as evidence of no clinical effect given the small sample size. All efficacy analyses on descriptive outcomes will be performed based on a mITT principle.

1. PTSD Symptom Sub-Scales
  - a. Descriptive statistics for the change in score from baseline to one month on the three PTSD symptom sub-scales (intrusions, hyperarousal, and avoidance) and confidence intervals will be provided for each treatment group.
  - b. Change in score from baseline to one month on the three PTSD symptom sub-scales (intrusions, hyperarousal, and avoidance) will be compared between mifepristone and placebo using two-sample t-test (or Wilcoxon rank-sum test if the normality assumption does not hold).
2. Depression
  - a. Descriptive statistics for the change in score from baseline to one month on the Beck Depression Inventory (BDI) and confidence intervals will be provided for each treatment group.
  - b. Change in score from baseline to one month on the Beck Depression Inventory (BDI) will be compared between mifepristone and placebo using two-sample t-test (or Wilcoxon rank-sum test if the normality assumption does not hold).
3. PTSD Symptom Severity

- a. Descriptive statistics for the change in score from baseline to one month on the PTSD Checklist (PCL) and confidence intervals will be provided for each treatment group.
- b. Change in score from baseline to one month on the PTSD Checklist (PCL) will be compared between mifepristone and placebo using two-sample t-test (or Wilcoxon rank-sum test if the normality assumption does not hold).
4. Sleep Quality
- a. Descriptive statistics for the change in score from baseline to one month on the Pittsburgh Sleep Quality Index (PSQI) and confidence intervals will be provided for each treatment group.
- b. Change in score from baseline to one month on the Pittsburgh Sleep Quality Index (PSQI) will be compared between mifepristone and placebo using two-sample t-test (or Wilcoxon rank-sum test if the normality assumption does not hold).
5. Anger
- a. Descriptive statistics for the change in score from baseline to one month on the STAXI and confidence intervals will be provided for each treatment group.
- b. Change in score from baseline to one month on the STAXI will be compared between mifepristone and placebo using two-sample t-test (or Wilcoxon rank-sum test if the normality assumption does not hold).
6. Functional Impairment
- a. Descriptive statistics for the change in score from baseline to one month on the functional impairment measure (item 24) from the CAPS and confidence intervals will be provided for each treatment group.
- b. Change in score from baseline to one month on the functional impairment measure (item 24) from the CAPS will be compared between mifepristone and placebo using two-sample t-test (or Wilcoxon rank-sum test if the normality assumption does not hold).
7. Neuroendocrine
- a. Descriptive statistics for the change in score from baseline to one week following treatment, and baseline to one month and confidence intervals for plasma cortisol and ACTH levels will be provided for each treatment group.
- b. Change in plasma cortisol and ACTH levels from baseline to one week following treatment and baseline to one month will be compared between mifepristone and placebo using two-sample t-test (or Wilcoxon rank-sum test if the normality assumption does not hold).
- c. Mean plasma cortisol levels at one month will be compared between clinical responders (30% reduction in CAPS score) and non-responders using a t-test (or Wilcoxon rank-sum test if the normality assumption does not hold). This analysis will be limited to those on mifepristone only.
- d. Mean ACTH levels at one month will be compared between clinical responders (30% reduction in CAPS score) and non-responders using a t-test (or Wilcoxon rank-sum test if the normality assumption does not hold). This analysis will be limited to those on mifepristone only.
8. Mifepristone and its metabolites
- a. Descriptive statistics and confidence intervals for one week following treatment for plasma levels of mifepristone and its metabolites will be provided.
- b. Mean plasma levels of mifepristone and its metabolites at one week will also be compared between clinical responders (30% reduction in CAPS score) and non-responders using a t-test (or Wilcoxon rank-sum test if the normality assumption does not hold).
- c. A continuous mixed-effects model for longitudinal observations of CAPS scores will also be used adjusting for aforementioned baseline characteristics, indicator variable that contrasts

mifepristone vs. placebo, and plasma levels of mifepristone and its metabolites at one week to determine the effect of them on CAPS scores trajectories.

Although it is not listed as an outcome, the percentage of unique participants with concurrent psychotropic medication use change by 1 month and by 3 month (end of the trial) will be compared between mifepristone and placebo using chi-square tests. Concurrent psychotropic medication change is defined as seeking a rescue medication for those who are not on concurrent psychotropic medication prior to randomization, or seek a new psychotropic medication or require a dose increase for those on a stabilized regimen treating PTSD prior to randomization. Those analyses will also be based on mITT principle. Except the primary analysis of the primary outcome, all efficacy and safety analyses will be performed with a significance level of 5% for two-sided tests. Due to exploratory nature of the study, and the sample size was not powered on hypothesis testing framework, careful consideration is necessary when interpreting the significance of these results on the primary, secondary and descriptive outcomes. The results of the trial are considered to be hypothesis generating and are not to obtain definitive efficacy information. No adjustments for multiplicity on various secondary outcome measures are planned in this phase IIa trial. The lack of adjustment will be noted in the resulting manuscripts.

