#### 4.k. Outcome Assessment

The primary clinical outcome measure will be clinical response status at study endpoint (week 4), defined as a 30% or greater reduction in CAPS total score from baseline to week 4. Response status at week 12 will also be assessed as a secondary outcome measure. Total symptom severity during the prior week will be measured using the CAPS (Blake et al., 1995), a well-validated scale widely used in outcome studies of PTSD. PTSD symptom severity is calculated by summing the frequency and intensity rating of each of the 17 PTSD symptom items.

The secondary outcome measures will be the change in CAPS score from baseline to 1 week, 4 weeks and 12 weeks, the presence of clinical response as defined above at 12 weeks, and the percentage of study drug related AEs or SAEs.

The descriptive clinical outcome measures will be change from baseline to week 4 and week 12 for the following: the three PTSD symptom sub-scale scores from the CAPS, self-reported depression severity as measured by the BDI (Beck et al., 1996), PTSD symptom severity as measured by the PCL (Weathers et al., 1996), sleep quality as measured by the PSQI (Buysse et al., 1989), self-reported experience, expression, and control of anger as measured by the STAXI (Spielberger et al., 1988), and functional impairment as measured by item 24 of the CAPS.

Neuroendocrine outcomes include change from baseline to post-pulse treatment in plasma cortisol and ACTH levels. These will allow for assessment of the acute neuroendocrine response to 600 mg of mifepristone and its relationship to treatment outcome. Additionally, plasma levels of mifepristone and its metabolites will be assessed immediately after one week of treatment.

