Albuquerque has been one of the top recruitment sites for two CSP studies in PTSD: CSP 563 (“Prazosin and Combat Trauma”, having recruited 12 participants in 11 months) and CSP 504 (“Risperidone Treatment for Military Service Related Chronic PTSD”, 14 participants in 30 months). Recruitment was also high in other PTSD studies. However due to low recruitment in this study, this site was terminated in March, 2015. Salisbury and Little Rock were added in April 2015, instead, to help recruitment.

Salisbury VAMC was a very successful site for CSP 563 (“Prazosin and Combat Trauma”). It is also home to a MIRECC dedicated to the study of post-deployment mental health problems including PTSD and mTBI. It has a full research infrastructure and ready-access to the study group of interest.

Little Rock VA has just successfully recruited for and completed several studies of PTSD focused on a similar participant pool. One was a randomized controlled trial of modafanil in OEF/OIF combat veterans with PTSD (25 subjects completed the RCT over an 18 month recruiting period). [name], the site investigator, was also the collaborating psychiatrist on “Telemedicine-based collaborative care for posttraumatic stress disorder: a randomized clinical trial” and facilitated a study examining psychophysiological measures in OIF/OEF veterans.

We propose to enroll 90 participants across multiple VA sites to yield 72 completers based on an estimated attrition rate of 20%. We expect the 3 active sites (Bronx, San Diego, and Durham) to enroll 25~26 patients each over the course of 31 months (0.8 per site per month); and the 2 added sites (Salisbury and Little Rock) to enroll 5~6 patients each over the course of 9~10 months (0.5~0.6 per site per month). The Albuquerque site that was terminated in February 2015 enrolled a total of 2 participants.

Given the data provided by the VHA Support Services Center and the individual study sites, this recruitment goal, which takes into account the challenges of recruiting unmedicated veterans and stably medicated veterans, is feasible.

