##### Primary Outcome:

Primary Analysis of Primary Outcome -The primary analysis for this study will not be based on a hypothesis test; rather, responder rates at one month will be calculated for each of two groups. If mifepristone 600 mg is observed to have at least a 15% higher responder rate than placebo, then we are at least 90% certain we have detected a clinically relevant signal. This analysis will be performed based on a modified intent-to-treat (mITT) principle. All randomized participants will be included in the analyses except for those for whom there is positive proof that they did not take a single dose of study medication (e.g. medication never picked up, full bottle returned, patient immediately declines participation after study medication has been dispensed) or there is positive proof that they are deemed ineligible after randomization and are terminated in the 7-day treatment phase due to safety concern. For patients who do not have one-month CAPS total score, their responses will be estimated using multiple imputation technique as outlined in Molenberghs and Kenward, 2007, Chapter 9 and implemented in the SAS procedure MI using participants aforementioned baseline characteristics and available information at other time points (baseline, 1 week, 12 week). The imputation will be done within each treatment group.

Secondary Analysis of Primary Outcome -The primary outcome will also be compared using chi-square tests. Additionally, logistic regression models will be used to adjust for aforementioned baseline characteristics. The model selection will use a backward elimination procedure and be verified by a forward selection procedure.

Exploratory Analysis of Primary Outcome -The primary outcome will also be explored for subgroups as defined by concurrent psychotropic medication use status and classification prior to randomization. The mITT principle will also be applied in the secondary and exploratory analyses of the primary outcome.

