Sensitivity Analysis of Missing Data- In the analyses mentioned above, missing data will be replaced using three additional procedures. The first procedure will entail the assumption of “worst case scenario” where the participants with missing data at week 4 will be deemed non-responders. This approach will provide a conservative test of treatment effects. In the second procedure, the last available information about the primary outcome, if available at week 1, will be used to impute the missing data at week 4 and if missing at both week 1 and 4, participants will be deemed non-responders. The third procedure involves the comparison on all participants whose CAPS score are obtained on week 4.

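### Six descriptive outcomes carry an mITT label but are tested on observed one-month change only; a baseline-adjusted mixed model would use the data already collected (minor)

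*Protocol*

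**What the plan says.** All references are to the protocol.

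- **Population.** Section 4.p.1, Descriptive Outcomes: "All efficacy analyses on descriptive outcomes will be performed based on a mITT principle". The mITT rule is under Primary Outcome: "All randomized participants will be included in the analyses except for those for whom there is positive proof" of no dose taken, or of ineligibility leading to termination for safety in the 7-day treatment phase. Missing the week-4 visit is not an exclusion.
- **Test.** Taking the BDI as the example: "Change in score from baseline to one month on the Beck Depression Inventory (BDI) will be compared between mifepristone and placebo using two-sample t-test", with a Wilcoxon fallback. Items 1b and 3b to 6b follow the same pattern.
- **Missing data.** Under Primary Outcome: "For patients who do not have one-month CAPS total score, their responses will be estimated using multiple imputation technique". The sensitivity paragraph there opens "In the analyses mentioned above, missing data will be replaced using three additional procedures", and all three procedures concern the week-4 CAPS response. Under Secondary Outcomes, the mixed model assuming missing at random is for CAPS scores at weeks 1, 4 and 12.
- **Attrition.** The Recruitment and Feasibility section plans 90 participants "to yield 72 completers based on an estimated attrition rate of 20" percent.
- **Time points.** Section 4.k: "The descriptive clinical outcome measures will be change from baseline to week 4 and week 12". Table 2 schedules CAPS and the self-reports at baseline and weeks 1, 4 and 12.

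**The concern.** The protocol fixes both a population and a test for these outcomes. Without a missing-data step between them, the two do not fit. A change score needs a week-4 value. Someone who attends week 1 and then leaves is in the mITT population, has a baseline and a week-1 score on each measure, and drops out of each one-month test.

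Two things are at stake. Precision is lost because baseline and week 1 are ignored. And if leaving depends on early response, the arm difference among those who stay is not the mITT difference, yet it would be reported under the mITT label. These comparisons are tested at two-sided 5%, and their pattern may inform whether a larger trial is pursued.

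A smaller mismatch runs alongside. Section 4.k defines these outcomes at weeks 4 and 12, and the lead-in to Descriptive Outcomes promises descriptive statistics to three months, but each itemised comparison in items 1 to 6 stops at one month.

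**Working it through.** **1. The plan's own figure.** 90 × (1 − 0.20) = 72 completers, or 36 per arm if losses are even. So at most 90 − 72 = 18 participants could lack a week-4 value. That is an upper figure, because the 20% is planned attrition for a 12-week study. The protocol gives no effect size, SD or correlation for the descriptive outcomes, so those below are assumptions.

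**2. One participant with a week-1 score but no week-4 score.**

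| Analysis | What the protocol provides | Contributes? |
|---|---|---|
| One-month CAPS response | Multiple imputation within arm | Yes |
| CAPS trajectory | Mixed model, missing at random | Yes, through week 1 |
| Items 1b to 6b | t-test or Wilcoxon on one-month change | No, as written |

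**3. Precision when loss is unrelated to outcome.** Assume a common SD σ, correlation 0.6 between baseline and each later visit, 0.75 between weeks 1 and 4, 45 per arm, and 20% lost after week 1 (36 left per arm).

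- Variance of change = 2(1 − 0.6)σ² = 0.80σ². SE of the t-test difference = √(2 × 0.80/36) σ = 0.2108σ.
- Week-4 variance given baseline = (1 − 0.36)σ² = 0.64σ².
- R² on baseline and week 1 = (0.36 + 0.5625 − 2 × 0.6 × 0.75 × 0.6)/(1 − 0.36) = 0.5977, leaving 0.4023σ². Week 1 thus explains 0.64 − 0.4023 = 0.2377σ² beyond baseline.
- Likelihood SE ≈ √[2(0.4023/36 + 0.2377/45)] σ = 0.1814σ.
- Ratio 0.2108/0.1814 = 1.16. With σ = 15 the SEs are 3.16 and 2.72. A simulation of this setting gave 3.15 and 2.73, a ratio of 1.15. Put the other way, the likelihood SE is about 13% smaller.
- Baseline adjustment alone, on week-4 completers: √(2 × 0.64/36) × 15 = 2.83. So of the gain of 3.16 − 2.72 = 0.44, about 0.33 comes from baseline and 0.11 from week 1.

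**4. Bias when loss depends on week-1 change.** Same correlations, σ = 15, true effect 8 points, the same logistic drop-out rule in both arms.

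- Repeated simulations, differing in the assumed week-1 effect, gave a t-test estimate of 7.15 to 7.4 (SE about 3.0). Shrinkage is 1 − 7.4/8 = 8% to 1 − 7.15/8 = 11%. At 7.15, drop-out was 24% on placebo and 14% on drug.
- The estimator using baseline and week 1 gave 7.95 to 8.02 (SE about 2.7).
- With half the dependence, one run of the t-test gave 7.67, a shrinkage of 4%.

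**5. Direction.** Standardised change, assumed true effects of 0.4 and 0.6 SD, about 20% lost overall, loss driven by the change itself. Entries are the share of the true effect retained by the observed-case difference.

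| Who leaves | 0.4 SD | 0.6 SD |
|---|---|---|
| Random, both arms | 1.01 | 1.00 |
| Common graded rule (logit slope 1.0 per SD) | 0.89 | 0.89 |
| Worst 20% within each arm | 0.99 | 1.00 |
| Worst 20% on placebo, random 20% on drug | 0.13 | 0.42 |
| Worst 20% on drug, random 20% on placebo | 1.88 | 1.58 |

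The last two rows are extremes and show direction only. Because loss there depends on the unseen outcome, a missing-at-random model would not fully repair them.

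**6. Can the test and the label coexist?** Yes, with imputation. With a true difference of 0.50 SD, a week-1 to week-4 correlation of 0.7 and about 20% missing according to week 1, the observed-case difference averaged 0.47 SD. Within-arm multiple imputation followed by the same two-group contrast averaged 0.50 SD on all 90.

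**The case against.** The strongest reply is that mITT, as defined here, says who belongs in the analysis and not how a missing value is filled. Missing-data rules for descriptive outcomes are often left to the SAP, which is not at hand. A reader might infer that these are declared completer analyses, or that a t-test cannot include those who leave. The document says neither, and step 6 shows that a t-test on imputed values works. That part of the reply stands, so this is not a proven contradiction. What remains is that the protocol does name a method for these items, and the method is unadjusted and ignores week 1.

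A reader might also infer that the plan hides a real drug effect. Step 5 does not support this: loss of non-improvers can shrink, leave alone or inflate the difference. Section 4.g allows treatment adjustment in order to prevent drop-out and does not require withdrawal. Section 4.e keeps those taken off treatment for an adverse event in follow-up. Section 4.h asks those who exit during acute treatment for an assessment three weeks after the last dose, although someone who leaves between weeks 1 and 4 is not covered by that request.

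The 20% is a planning figure from other studies, with nothing on timing. The bias in step 4 is modest: 0.6 to 0.85 points against an SE of about 3. The SD of 15 exceeds the pilot SDs in Table 1 for the BDI and the CAPS sub-scales, so the point values do not carry over to them, although the SE ratio in step 3 does not depend on the SD. Finally, the protocol calls the results hypothesis generating and warns against reading non-significance as no effect.

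**Conclusion.** The point holds in limited form. As written, items 1b to 6b use only participants with a week-4 value, ignore week-1 scores and do not adjust for baseline, while carrying an mITT label.

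The firm consequence is lost precision: a standard error roughly 15% larger than a likelihood model would give, under correlations of 0.6 and 0.75 and 20% random loss after week 1. About three quarters of that comes from ignoring baseline. Bias is conditional on drop-out following early response, and its sign depends on which arm loses its non-improvers. One assumed common rule gives 8 to 11% shrinkage; loss of non-improvers mainly on drug gives inflation.

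The one-month responder rule does not use these outcomes, so the severity is minor.

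**What to change.** In items 1b to 6b, make the main comparison a likelihood-based mixed model of the kind already planned for CAPS. Use categorical visit (weeks 1, 4, 12), arm, arm-by-visit and baseline score, and include every mITT participant with at least one post-baseline score. The CAPS model is described through a group-by-time slope, so categorical visit and baseline score must be stated explicitly. Report the week-4 arm difference, and the week-12 difference to match section 4.k. Report how many mITT participants have no post-baseline score.

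Keep the t-test or Wilcoxon test as a check labelled observed-case. This also guards against non-normality, for instance in the single CAPS item 24. If the sponsor prefers to keep the t-test as the main analysis, it should either extend the within-arm imputation to these measures or drop the mITT label for them.

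The cost is a few lines of protocol or SAP text and standard programming, with no new data. The downside is reliance on missing at random, which the CAPS model already assumes.

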Additionally, the clinical research assistant will be responsible for contacting the study participant in-between visits via telephone (i.e., week 2 (visit 3), week 6 (visit 5), week 8 (visit 6), and visit 10 (visit 7)) so that contact will be made with the participant at least every two weeks. Week 2 has a  $\pm 2$  day window for visit scheduling, while weeks 6, 8 and 10 each have a  $\pm 5$  day window for visit scheduling. Through this telephone check-in, site investigators will be able to monitor safety, obtain PTSD symptom ratings, and identify any signs of deterioration. To assess PTSD symptoms longitudinally, the PCL will be administered at every in-person study visit and will be administered by telephone at each biweekly check-in. The study participants will be given a laminated card with the PCL on it to take home and will indicate their responses to the clinical research assistant who will record them; it is estimated that this would take ten minutes or less. This telephone check-in should also help enhance retention. A script will be developed for the telephone check-ins so they are standardized across time and site.

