|                   | C-SSRS                                                                                                                       | X                                                         |          |                 | X                | X                                  | X                 |
| Clinical Outcomes | PTSD Symptoms (CAPS past week, past month)                                                                                   |                                                           | X        |                 | X                | X                                  | X                 |

|                |                                                  |  |   |                                              |   |   |   |
|----------------|--------------------------------------------------|--|---|----------------------------------------------|---|---|---|
|                | Self-Reports (including PCL)                     |  | X |                                              | X | X | X |
|                | Alcohol Consumption                              |  | X |                                              | X | X | X |
| Neuroendocrine | Plasma cortisol, ACTH †               |  | X | X (only plasma cortisol will be collected**) | X | X |   |
|                | Plasma mifepristone and metabolites ‡ |  |   |                                              | X |   |   |

\*Glucose, electrolytes, creatinine and liver function tests may be ordered together by requesting the comprehensive metabolic panel.

\*\*For cortisol collection at day 3, the samples will be centrifuged on site, aliquoted into labeled cryovials, and stored frozen in a deep freezer (-80 degrees Celsius) until shipped in batches to the Core Lab. In the case of a significant AE/ SAE a cortisol determination will be made at the local lab.

† The blood tubes for neuroendocrine testing (cortisol and ACTH) will be centrifuged on site, aliquoted into labeled cryovials, and stored frozen in a deep freezer (-80 degrees Celsius) until shipped to the Core Lab.

‡ Blood samples of mifepristone and its metabolites will be de-identified and labeled with participants' study ID numbers, draw date, and draw time. The blood tube will be centrifuged on site, aliquoted into labeled cryovials for 1 ml of plasma, and stored frozen in a deep freezer (-80 degrees Celsius) until shipped to MicroConstants

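### The PCL is scheduled at seven post-baseline contacts for a longitudinal purpose, but its only itemised between-arm analysis is a one-month t-test, and items 1–6 leave out the week-12 time point that section 4.k defines.

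*Protocol*

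**What the plan says.** Protocol 4.f gives the purpose and frequency of the PCL: "To assess PTSD symptoms longitudinally, the PCL will be administered at every in-person study visit and will be administered by telephone at each biweekly check-in". That section sets the telephone contacts at weeks 2, 6, 8 and 10. One of these is printed as visit 10, but the scheduling-window sentence that follows, and 4.i, show that week 10 is meant. Table 2 marks the self-reports, PCL included, at baseline and at weeks 1, 4 and 12. Section 4.f also gives the calls an operational use: through them "site investigators will be able to monitor safety, obtain PTSD symptom ratings, and identify any signs of deterioration".

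Protocol 4.k fixes the time points of the descriptive clinical outcomes, PCL among them: "The descriptive clinical outcome measures will be change from baseline to week 4 and week 12 for the following".

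Protocol 4.p.1, Descriptive Outcomes, opens with a general rule: description with confidence intervals at one month and at three months for every descriptive measure, plus comparisons between arms with no time point attached. The itemised list follows. Items 1 to 6 (CAPS sub-scales, BDI, PCL, PSQI, STAXI, CAPS item 24) each name one month only, both for the description (a) and for the comparison (b). For the PCL, item 3b reads: "Change in score from baseline to one month on the PTSD Checklist (PCL) will be compared between mifepristone and placebo using two-sample t-test", with a rank-sum test as the fallback.

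The longitudinal models in 4.p.1 (under Secondary Outcomes and in item 8c) are for CAPS.

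**The concern.** There are two linked problems.

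First, an instrument administered repeatedly in order to follow symptoms over time is assigned a single-visit t-test of change, without baseline or site in a model, and nothing is specified for most of the scores. Sections 1.b and 4.g justify the three-month follow-up by the wish to learn whether the effect of a one-week pulse lasts. CAPS is measured at weeks 1, 4 and 12. The PCLs at weeks 6, 8 and 10 are the only symptom-scale scores scheduled between weeks 4 and 12, so they alone could show the course in that interval.

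Second, the protocol is inconsistent on week 12. Section 4.k and the opening of the Descriptive Outcomes include it, while items 1 to 6 do not.

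At stake are a clear description of how symptoms evolve after week 4 and protection against a later choice among several possible PCL time points. That protection matters somewhat because 4.p.1 plans no multiplicity adjustment for the secondary measures.

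**Working it through.** **Step 1. Count the scheduled post-baseline PCL scores.**
- In person (Table 2): weeks 1, 4 and 12, which is 3.
- By telephone (4.f): weeks 2, 6, 8 and 10, which is 4.
- Total: 3 + 4 = 7. Taken literally, the 4.f wording on in-person visits would add day 3, but Table 2 leaves that cell blank, so 7 is used.

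**Step 2. Match each time point to a named analysis.**

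| Week | Description with interval | Itemised arm comparison |
|---|---|---|
| 1 | none named | none named |
| 2 | none named | none named |
| 4 | yes (opening rule and item 3a) | yes (item 3b) |
| 6 | none named | none named |
| 8 | none named | none named |
| 10 | none named | none named |
| 12 | yes (opening rule, with 4.k) | not itemised; the general comparison sentence names no time |

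Two of seven time points have a named analysis and five do not. In planned scores before attrition, 90 × 7 = 630, of which 90 × 5 = 450 have none. Among the 72 completers assumed in 4.n.2, the second figure is 72 × 5 = 360.

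**Step 3. Look for other uses.** The mixed models concern CAPS. The multiple imputation for the primary outcome draws on information at baseline, week 1 and week 12; it does not name the PCL or the telephone weeks.

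**Step 4. Set the week-12 texts side by side.** Section 4.k has "change from baseline to week 4 and week 12 for the following", and a list that includes the PCL. The opening of the Descriptive Outcomes promises one-month and three-month description. Items 1 to 6 give one month for both parts (a) and (b). Where more than one time point was meant, 4.p.1 names them: item 7b gives one week and one month, and the medication-change comparison gives one month and three months. The natural reading of items 1 to 6 is therefore month one only, which conflicts with 4.k.

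**Step 5. What averaging could add in precision.** The protocol gives no within-person correlation r, so r = 0.6 to 0.8, equal at all lags, is an assumption. For the mean of the five raw scores at weeks 4, 6, 8, 10 and 12 against one score, the ratio of standard errors of the arm difference is √((1 + 4r)/5).
- r = 0.6: √(3.4/5) = √0.68 = 0.825, about 18% smaller.
- r = 0.8: √(4.2/5) = √0.84 = 0.917, about 8% smaller.

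The two standard errors belong to different quantities: one to the average difference over weeks 4–12, the other to the difference at a single visit. If the effect fades after week 4, the average is also a smaller effect.

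**The case against.** Much of the case on the other side is sound. The SAP is not at hand, and modelling a descriptive self-report measure at extra time points is often left to it. Section 4.f states why the PCL is collected; it does not promise a longitudinal analysis. On that ground alone, the absence of a PCL model would be a weak point. What remains is that the protocol does fix a method for the PCL, a single-visit t-test, and that its own sections disagree on week 12.

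Several stronger readings are tempting but not supported:
- A reader might infer that the telephone scores are wasted. They are not: 4.f, and 4.i again, give them a monitoring use. What they lack is a named statistical analysis.
- A reader might infer that week-12 PCL is ignored. The opening of the Descriptive Outcomes has it described with confidence intervals, and the general sentence on comparisons could be read to cover it.
- A reader might infer that 4.k promises a week-12 comparison between arms. It defines outcome measures and says nothing about testing.
- A reader might infer that durability goes unexamined. The 12-week responder rate and the CAPS mixed model address it on the clinician-rated scale. The PCL would add the course between weeks 4 and 12.
- A reader might turn Step 5 into 19–47% more participants (1/0.84 = 1.19 and 1/0.68 = 1.47). That treats the week 4–12 average as if it were the week-4 difference and rests on an assumed correlation.

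Two cautions about pooling also stand. Telephone scores are spoken to the research assistant from a card, unlike the in-person self-reports. Treatment adjustments are discouraged most in the first month (4.g), so later scores may reflect more of them.

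**Conclusion.** The point holds in a limited form. The gap between purpose and analysis (two of seven post-baseline PCL time points covered) and the week-12 inconsistency across items 1 to 6 both follow from the protocol text without any assumption. A baseline-adjusted repeated-measures model is a better use of scores already collected than the t-test in item 3b. The size of any precision gain is not known from the documents: the 8–18% figure depends on the assumed equal correlation of 0.8 to 0.6 and applies to the averaged raw-score difference only.

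The consequence is small. These outcomes are descriptive, the trial is declared hypothesis-generating, and the primary responder rule at week 4 is untouched. The change is worthwhile but optional.

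**What to change.** 1. Replace item 3b with one repeated-measures model of all post-baseline PCL scores, with visit as a category, arm, arm-by-visit interaction, baseline PCL and site. Report arm differences with confidence intervals at weeks 4 and 12. Report the week 4–12 average as an additional quantity, labelled as distinct from the week-4 difference.
2. Reconcile items 1 to 6 with 4.k and with the opening of the Descriptive Outcomes by stating the week-12 description and the week-12 comparison in each item.
3. Add a sentence that telephone and in-person administrations are pooled and that later scores may reflect treatment adjustments, so that both are kept in mind in interpretation.

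The cost is wording in the analysis section (or in the SAP, if it is still open), settled before unblinding. No new data, visits or participants are needed.
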